**Methods:**

The Enhancing the A in SAFE (ETAS) study is a community randomized intervention costing and community acceptability study. Following a population-based trachoma prevalence survey in 1 county, 30 communities will be randomized 1:1 to receive 1 of 2 enhanced MDA interventions, with the remaining communities receiving standard-of-care annual MDA. The first intervention strategy will consist of a community-wide MDA followed by 2 rounds of targeted treatment to children ages 6 months to 9 years, 2 weeks and 4 weeks after the community MDA. The second strategy will consist of a community-wide biannual MDA approximately 6 to 8 months apart. The costing analysis will use a payer perspective and identify the total cost of the enhanced interventions and annual MDA. Community acceptability will be assessed through MDA coverage monitoring and mixed-methods research involving community stakeholders. A second trachoma-specific survey will be conducted 12 months following the original survey.

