## Methods

### Study design overview

The Enhancing the A in SAFE (ETAS) study is a community randomized study to evaluate cost and community acceptability of enhanced antibiotic trachoma interventions within an endemic county in South Sudan. A population-based prevalence survey will be conducted whereby 30 communities are selected for trachoma assessment. Following the survey, communities will be randomized 1:1 to receive 1 of 2 enhanced antibiotic interventions (Fig. 1). The remaining communities in the county will receive standard-of-care annual MDA. The primary outcomes of the study are the cost of enhanced MDA compared to standard-of-care annual MDA and the community acceptability of enhanced MDA within study communities. A trachoma impact survey will be conducted approximately 12 months following the original trachoma prevalence survey. The total study duration will be approximately 13 months from the start of the community-level census to the time of the 12 month follow up impact survey. This protocol adheres to the Standard Protocol Items: Recommendations for Interventional Trials (SPIRIT) guidelines and refers to version 1.2 of the study protocol as revised 5 May 2021.

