### Setting, eligibility, and participants

The study will be conducted within a trachoma endemic county in Eastern Equatoria state, South Sudan (Fig. 2). This area was chosen based on previous survey data demonstrating a high burden of TF among children ages 1 to 9 years ranging from 30 to 48% [7]. The baseline for this study will be timed to coincide with the scheduled programmatic trachoma impact surveys in Eastern Equatoria state. For purposes of this manuscript, the initial survey connected to this study will be referred to as a baseline survey and the survey conducted at completion of the study will be referred to as an impact survey (survey methods described below). As part of the baseline survey to determine TF prevalence in the study county, 30 communities will be randomly selected from a geographically ordered list provided by the South Sudan MOH Trachoma Control Program [8]. All 30 communities will be enrolled in this randomized community study. Communities are eligible to participate if they are in the study county regardless of the individual-community level TF prevalence. There are no exclusion criteria for community-level participation. Within study communities, all households and individuals will be eligible for participation. Children ages 6 months to 1 year will be eligible for azithromycin interventions in this study as they are normally targeted with this medication as part of programmatic interventions and in previous randomized trials, they could potentially serve as an infection reservoir if not treated and are an age group which may benefit from the ancillary effects of azithromycin on mortality [9–13]. Because of the observed mortality benefit to these young children, ongoing studies are now randomizing children in this age group to multiple doses of azithromycin per year at national levels [14].

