**Fig. 2 Fig2:**
[figure not shown]
ETAS study area in Eastern Equatoria state, South Sudan with 2015 TF prevalence estimates shown

For the 30 communities enrolled in the randomized community study, we expect an average population per community (based on programmatic data) of 649 individuals. This would lead to MDA treatment data on approximately 19,470 individuals of all ages. Since children ages 6 months to 9 years account for approximately 40% of the population, we expect to have MDA treatment data on 260 children per cluster or 7,788 total children in this age range.

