The economic cost of capital items, i.e. those only incurred once and with a value of 100 USD or more, will be annualized based on a 3% discount rate and estimates of the useful life of the item [22]. A “useful life” is defined as the period during which an asset or property is expected to be usable for the purpose it was acquired. For vehicles specifically, we will calculate the daily cost of a vehicle in relation to its useful life and discount rate. The financial costs of capital items will be estimated by dividing by the number of years of useful life without discounting (straight line depreciation). Rental costs will be used to determine the cost of office buildings. If a building is owned, the rental cost will be used as a cost indicator. Recurrent costs will be disaggregated from The Carter Center budget and assigned to the cost data categories for each treatment arm after each intervention phase as well as the standard-of-care annual MDA. Personnel costs will include participation in the intervention (e.g., per diems), as well as the relevant share of that person’s salary and fringe benefits that cover their working time as part of the intervention [23]. The proportion of salaries and benefits that are attributable to MDA activities will be estimated by program staff.

Commodities include the study drug, Zithromax®, which is donated, as well as TEO, which is purchased by The Carter Center. The cost of TEO will be included as a financial and economic cost. The economic costs of donated medicines will also be calculated. List costs will be derived from the International Medical Products Price Guide [24].

To estimate the costs associated with a programmatic setting, study and research costs will be removed to make costs comparable to the control communities. These costs would be those associated with increased supervision and monitoring, increased training for data collection, data collection, and administration of the study, and they will be separated among other costs. Further analysis will use the costs associated with the 2 intervention delivery methods and will estimate the potential costs incurred if each intervention was scaled up region- or country-wide. This will be calculated by multiplying the unit cost per person treated by the number of people requiring antibiotics, as stated in the WHO Alliance for the Global Elimination of Trachoma by the year 2020 (GET2020) database [25].

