#### Economies of scale

Costing analyses of MDA programs often assume an intervention’s cost per treatment is constant, regardless of the number of individuals treated. This is a misleading way to consider the delivery costs of MDA, due to the occurrence of economies/diseconomies of scale [28]. This analysis will explore the effect of economies of scale by presenting the cost per person treated at 3 different coverage levels (60%, 80%, 90%).

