This study will utilize two MDA strategies that represent enhancements to the standard-of-care annual MDA. In a previous 3-country study, it was demonstrated that a 3-dose strategy could drastically reduce ocular *Ct* infection among children [11]. Treating communities with multiple rounds within a short period of time could be programmatically favorable as it would allow for a single drug shipment and a single training prior to intervention. Targeting children may also be more cost effective as it requires less medication than a community-wide MDA and yet targets the age group shown to act as an infection reservoir within communities [9, 11, 32]. Recently a modeling study demonstrated the efficacy of this 3-dose, targeted strategy on *Ct* infection, however, it has yet to be implemented within actual communities. The second enhanced MDA strategy in this study, biannual MDA, has been compared to annual MDA in several randomized trials conducted in Ethiopia [35, 36]. Although biannual MDA has not shown to be statistically significantly more effective than standard-of-care annual MDA in these past trials, a faster time to elimination in some communities was observed. Examining the cost and community acceptability of these enhanced MDA strategies in a real-world setting will provide valuable data to better understand the programmatic implications of increasing the frequency and targeting of MDA interventions.

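### The enhanced-versus-annual cost comparison may partly reflect campaign scale, because the extra rounds are costed in only 15 communities per arm and no planned step separates strategy from the number of communities served

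*Protocol article*

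**What the plan says.** Study design overview states: "The primary outcomes of the study are the cost of enhanced MDA compared to standard-of-care annual MDA", alongside community acceptability. The abstract gives the allocation: "30 communities will be randomized 1:1 to receive 1 of 2 enhanced MDA interventions, with the remaining communities receiving standard-of-care annual MDA". That is 15 communities per enhanced arm. Under Setting, eligibility, and participants, the study communities are drawn across the county: "30 communities will be randomly selected from a geographically ordered list".

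The Interventions section makes the extra rounds separate deployments. One arm has two child-only rounds, 2 and 4 weeks after the community-wide round. The other has a second community-wide round at least 6 months after the first.

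Intervention costing defines unit cost as total cost divided by people treated. It takes comparator costs from 15 randomly chosen annual-MDA communities, using the same collection methods. For the programmatic setting it adds that "study and research costs will be removed to make costs comparable to the control communities". The items removed are extra supervision and monitoring, extra training for data collection, data collection itself, and study administration.

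Economies of scale says that assuming a constant cost per treatment is misleading, then plans to show unit cost at 60%, 80% and 90% coverage. Sensitivity analysis varies drug, delivery, security and per diem costs, useful life and the discount rate, and removes COVID-19 protective equipment.

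**The concern.** The comparator is costed inside a larger operation: "The remaining communities in the county will receive standard-of-care annual MDA". An extra round is costed as an operation for 15 communities. Some costs of a round, such as planning, a training or a drug shipment, may not shrink in proportion to the number of communities served. To that extent the extra rounds carry more cost per person for a reason that belongs to the trial layout and not to the strategy.

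The stated safeguards do not reach this. The removed items are research costs, and planning, transport, sensitisation and routine supervision of a 15-community round are delivery costs that stay in. Costing 15 comparator communities equalises the number costed, not the size of the campaign whose shared costs they carry. The scale analysis changes how many people are treated within a community, not how many communities a round serves.

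The programmatic cost is meant to inform Ministry of Health resource allocation, and the Discussion promises an answer on affordability. A programme adopting either strategy would presumably run it more widely than in 15 communities. The same unit cost is also the multiplier in the planned region- or country-wide projection.

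**Working it through.** **The plan's own figures.** The article gives an "average population per community (based on programmatic data) of 649 individuals" and about 40% of the population aged 6 months to 9 years.
- All 30 communities: 30 × 649 = 19,470 people; 19,470 × 0.40 = 7,788 children; 649 × 0.40 = 259.6 children per community. All three agree with the article (19,470; 7,788; 260).

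**Size of the extra rounds (15 communities).**
- Second biannual round: 15 × 649 = 9,735 people.
- Each child-only round: 9,735 × 0.40 = 3,894 children.

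**Reach of the planned scale analysis.** 0.90 / 0.60 = 1.5-fold in people treated, with the number of communities unchanged.

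**Illustration of what is left out.** Two inputs are not in the article and are assumed here: K, the number of communities in the county, and f, the share of the annual round's unit cost that is fixed per round. Annual MDA is taken as a campaign in the K − 30 remaining communities. The 30 study communities plus 15 comparator costing sites imply only that K is at least 45.

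The ratio is the unit cost of the round in 15 communities to the unit cost of the same round at the annual campaign's scale.
- Second biannual round: f × (K − 30)/15 + (1 − f).
- Child-only round: [f × (K − 30) × 649/3,894 + (1 − f)] / [f/0.40 + (1 − f)].

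Example with K = 60 and f = 0.3. Biannual: 0.3 × 2 + 0.7 = 1.30. Child-only: (0.3 × 19,470/3,894 + 0.7)/(0.75 + 0.7) = 2.20/1.45 = 1.52.

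| K (assumed) | (K − 30)/15 | Biannual, f = 0.1 to 0.5 | Child-only, f = 0.1 to 0.5 |
|---|---|---|---|
| 45 | 1.0 | 1.00 | 1.00 |
| 60 | 2.0 | 1.10 to 1.50 | 1.22 to 1.71 |
| 100 | 4.7 | 1.37 to 2.83 | 1.80 to 3.62 |
| 200 | 11.3 | 2.03 to 6.17 | 3.25 to 8.38 |

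For comparison, take 80% coverage as the reference. Moving from 90% to 60% changes unit cost by (f × 0.8/0.6 + 1 − f)/(f × 0.8/0.9 + 1 − f), which is 1.04 at f = 0.1 and 1.24 at f = 0.5.

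The table shows how the effect depends on two unknowns; it does not estimate the effect in this county. It starts at no effect (K = 45), and any f below 0.1 brings every row closer to 1.

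**The case against.** The strongest reply is that the costing method already absorbs part of the problem. Intervention costing charges vehicles by the day and salaries by the share of working time, so a small round that uses fewer vehicle-days and staff-days is charged less. That lowers any plausible f, and it stands. Training and shipment may still be indivisible, but nothing in the article supports a particular fixed share. Supplemental Table S1 and the full protocol (version 1.2) are not shown and may hold the allocation rule for shared costs, so its absence from the article is not itself a fault. The price-based sensitivity analysis also gives some range for programme cost, though it does not isolate the number of communities served.

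A reader might infer three stronger things that the article does not support.
- **A scale gap of at least threefold.** This comes from 45/15 = 3.0 and needs the first round in the study communities and annual MDA elsewhere to be one 45-community campaign. The article does not say so. For the remaining communities alone, the only documented floor is 15 against 15, a ratio of 1.0.
- **A distorted ranking of biannual against triple-dose.** Both arms have 15 communities. The Discussion's remark on closely spaced rounds, that "it would allow for a single drug shipment and a single training prior to intervention", describes a real feature of the strategy and not an artefact of scale. In the illustration the child-only rounds are inflated more than the biannual round, so a bias against biannual cannot be read off.
- **Shorter travel under annual MDA because teams work neighbouring communities.** The random draw spreads the study communities, but the article does not describe how annual-MDA teams move.

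**Conclusion.** The point holds as a limit on interpretation. The extra rounds are delivered and costed in 15 communities per arm, the comparator comes from the campaign in the rest of the county, and none of the planned steps separates strategy from the number of communities a round serves. The enhanced-versus-annual comparison may therefore partly reflect scale. The comparability wording claims more than removing research costs can deliver, and the scale analysis leaves out one of the dimensions that the article's own warning about constant unit costs covers.

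The size is unknown. It depends on the county's community count, the fixed-cost share and how shared costs are allocated. It could be negligible if the county is small or shared costs are apportioned by use, and substantial if neither is true. No direction is claimed for biannual against triple-dose.

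**What to change.** 1. Keep the observed cost as the primary result, since real-world cost is what the study sets out to measure.
2. In the micro-costing database, tag each item as fixed per round, per community visited, or per person treated.
3. In Economies of scale, add the number of communities served, from 15 up to county-wide, as a second axis beside coverage. Report all three strategies at one common county-wide scale next to the observed cost.
4. In Intervention costing, limit the comparability statement to research costs: removing them makes the arms comparable on research activity, not on campaign size.

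The cost is one extra tag on items already being recorded and a little more analysis. Randomization, treatment and fieldwork do not change. The drawback is that the common-scale figure is partly modelled and rests on the tagging, so it belongs beside the observed cost and not in its place.

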### Intervention costing

The costing analysis will determine the relative costs of the enhanced MDA strategies, including the triple dose and biannual MDA, which will be compared to each other, and compared to the standard-of-care annual MDA. This study will utilize the Global Health Cost Consortium Reference Case for Estimating the Costs of Global Health Services and Interventions and the Global Health Cost Consortium Principles and Methods Reporting Checklist to ensure the quality and comparability of results [20, 21]. The costing analysis will provide the evidence base to inform resource allocation decisions by the South Sudan MOH and partners within the country.

The study will take a payer perspective and encompass the costs incurred by The Carter Center as the technical and financial supporting implementing partner. This will be used to identify the cost per person treated and total costs associated with each arm of the study and annual MDA. To reduce the potential for bias, cost data will be collected using the same methods from 15 randomly selected communities in the study county receiving the standard-of-care annual MDA. Taking an ingredients-based approach, the study will include a detailed micro-costing database that captures all financial and economic costs incurred. The study will use the community level as the unit of analysis for total costs and calculate the unit cost per person treated using a top-down approach, dividing the total cost by the number of people treated.

The quantity and price of all required resources will be identified to evaluate total intervention costs for each arm of the study as well as the standard-of-care annual MDA (Table 1). To ensure costs such as salaried labor are not double counted, some activities that include staff time, including social mobilization and training, will not be broken down into all specific components. Salaried costs, for example, will be included under central administration and not included in each cost category. Where possible, data will be extracted from The Carter Center and South Sudan MOH databases.

**Table 1 Tab1:** Summary of activity costs included in each cost category within the ETAS study

Input/line item	Planning	Training	Community sensitisation	Drug transportation	Drug administration	Supervision	Surveillance	Reporting	Central administration
*Capital Costs*									
Buildings	x	x	x	x	x	x	x	x	x
Communication and IT equipment	x	x	x	x	x	x	x	x	x

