#### Sensitivity analysis

Univariate and multivariate sensitivity analysis will be conducted to identify main cost drivers and identify a range of potential program costs. The sensitivity analysis will explore changes to the cost of drugs, treatment delivery, security, and per diems, and assumptions around the useful life of capital items. Costs of personal protective equipment associated with COVID-19 prevention will be removed in the sensitivity analysis. The sensitivity of the discount rate will also be varied from 0–6%.

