### Community acceptability

#### Antibiotic coverage

Prior to the MDA interventions, a household census will be conducted in all 30 communities whereby all members of all households will be enumerated and the name, sex, and age of everyone will be recorded via electronic census forms. A household member is defined as any person who has lived for at least one month in the household and eats and sleeps in the household. Global positioning system (GPS) coordinates will be captured for each household. The study community census will be used to establish the population to be targeted for study interventions and will provide the denominator for MDA coverage calculations. New residents migrating into study areas after the census but prior to MDA treatment will be added to the census as they are detected. Further, residents unknown to the study team during the MDA treatment will also be added to the census and subsequently treated, if eligible.

During the MDA, each administered dose will be recorded into the electronic record created during the community census by a trained data collector who travels with the distribution team. This record will be used for both study arms to determine the antibiotic coverage during each of the subsequent treatment rounds, allowing for the calculation of the number of doses each participant received. The definition of coverage for this study is: the number of individuals ages 6 months to 9 years who received the drug in study communities in each treatment round divided by the number of children ages 6 months to 9 years enumerated in the baseline census. A secondary analysis will calculate the antibiotic coverage in each round for the age groups 10 to 15 years and ≥ 15 years. Further analyses on compliance will examine the extent and predictors of missed rounds among the 2 study arms.

The dataset on treatment coverage will be compiled quickly by the study coordinator and will be used to monitor the success of the intervention. If the coverage is lower than expected, < 85% among children ages 6 months to 9 years, the treatment team will be redeployed to conduct a community mop-up to improve treatment coverage.

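### The region- or country-wide cost multiplies one constant unit cost per person treated by the number in need, an assumption the protocol itself calls misleading and one that fits only 100% coverage

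*Protocol article*

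**What the plan says.** Four places in the protocol bear on this.

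- **Unit cost (Intervention costing).** The analysis will "calculate the unit cost per person treated using a top-down approach, dividing the total cost by the number of people treated".
- **Scale-up (Intervention costing).** A further analysis of the two enhanced strategies "will estimate the potential costs incurred if each intervention was scaled up region- or country-wide". The method is given in one sentence: "This will be calculated by multiplying the unit cost per person treated by the number of people requiring antibiotics". The count of people comes from the GET2020 database.
- **Economies of scale.** Costings of MDA programmes are said often to assume that the "cost per treatment is constant, regardless of the number of individuals treated". The protocol's judgement of that assumption is: "This is a misleading way to consider the delivery costs of MDA, due to the occurrence of economies/diseconomies of scale". Its response is to show the cost per person treated at 60%, 80% and 90% coverage.
- **Sensitivity analysis.** "The sensitivity analysis will explore changes to the cost of drugs, treatment delivery, security, and per diems". The useful life of capital items, the discount rate and COVID-19 protective equipment are varied as well. Programme size is not listed.

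Neither the scale-up text nor the Economies of scale section says that the coverage-specific unit costs enter the projection.

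**The concern.** The scale-up formula is linear in people. It takes a unit cost observed in 15 communities per arm (30 randomised 1:1) and applies it unchanged to a region or the country. That is the assumption which the Economies of scale section rejects, so the protocol fixes a formula that conflicts with its own reasoning.

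There is also a mismatch of bases. The unit cost is per person treated, while the multiplier counts people who need treatment, whether or not they would be reached. The two agree only if everyone is reached.

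At stake is a budget figure. The Intervention costing section says that the costing is meant to inform resource allocation by the Ministry of Health and partners, and the scaled cost is the output closest to that use. A reader who takes it as the expected cost of a programme run as in the study would be working from a different scenario without being told so.

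**Working it through.** The protocol gives no unit cost, scaled cost or number requiring antibiotics, so there is no cost figure to reproduce. The volume inputs do reproduce: 30 × 649 = 19,470 people, and 0.40 × 19,470 = 7,788 children, both as stated under Setting, eligibility, and participants.

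**1. Mismatch of bases.** Let R be the people requiring antibiotics, c the coverage and u the unit cost (total cost ÷ people treated).

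- Planned figure: u × R.
- Cost of a programme that reaches coverage c at the same unit cost: u × c × R.
- Ratio: (u × R) ÷ (u × c × R) = 1/c.

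| Coverage c | Source | Planned ÷ programme cost |
|---|---|---|
| 60% | Economies of scale | 1/0.60 = 1.67 |
| 80% | Economies of scale | 1/0.80 = 1.25 |
| 85% | Antibiotic coverage (mop-up trigger, children) | 1/0.85 = 1.18 |
| 90% | Economies of scale | 1/0.90 = 1.11 |
| 100% | not a scenario in the protocol | 1.00 |

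The 85% level is stated only for children aged 6 months to 9 years; using it for all ages is an assumption.

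**2. What the coverage scenarios can show.** Going from 60% to 90% coverage changes the number treated by 0.90/0.60 = 1.5-fold, in the same communities. It does not change how many communities share planning, training or central administration. It therefore cannot stand in for growth from 15 communities to a region or country.

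**3. Size of the scale error (illustration only).** Suppose a share s of the unit cost does not grow with programme size, and the programme expands K-fold. Then planned ÷ actual = K ÷ (s + (1 − s)K). Both s and K are assumptions; neither is in the document.

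| Assumed s | K = 10 | K = 100 |
|---|---|---|
| 10% | 10/9.10 = 1.10 | 100/90.10 = 1.11 |
| 25% | 10/7.75 = 1.29 | 100/75.25 = 1.33 |
| 50% | 10/5.50 = 1.82 | 100/50.50 = 1.98 |

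This covers economies of scale only. Diseconomies, which the protocol also names, would make the linear figure too low.

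**4. Counting unit.** The text divides by people, which reads as unique persons. If rounds were summed instead, the triple-dose strategy would give 1 + 2 × 0.40 = 1.8 treatments per person and the biannual strategy 2.0, at full uptake. At 85% coverage in every round, planned ÷ actual would then be 1/(0.85 × 1.8) = 0.65 and 1/(0.85 × 2.0) = 0.59. The choice of unit can thus reverse the sign of the error in step 1.

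**The case against.** The strongest reply is that the product is a coherent quantity: the cost of treating everyone in need at the observed unit cost. The protocol speaks of potential costs in a further analysis, and it does not say that the target is a programme at partial coverage. The Sensitivity analysis section also plans a range of programme costs. This stands, and it is why the formula cannot simply be called an error. But that reading still needs a unit cost that stays constant up to 100% coverage and across any number of communities. The protocol disputes this, and it names no 100% scenario.

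A reader might also draw three stronger conclusions, which the documents do not support.

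- **That the scaled costs will be wrong, and too high.** The document gives no fixed share. Salaries are apportioned by working time, vehicles are charged by the day and capital is annualised, so much overhead is already prorated to use. Diseconomies could reverse the sign.
- **That the enhanced strategies are penalised against annual MDA.** Annual MDA is costed by the same methods in 15 randomly selected communities, research costs are removed for comparability, and only the two enhanced strategies are scaled up.
- **That cost per person is understated by 44% (1 − 1/1.8) or 50% (1 − 1/2.0).** This follows only if people treated means treatments summed over rounds. The plain reading is persons, and the linked census and treatment record identifies them.

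It is also fair that the 60% row is a scenario and not an expectation. The protocol's own marker is "If the coverage is lower than expected, < 85% among children ages 6 months to 9 years", which points to a ratio of 1.18 or less in children if that level is met. Finally, an article may leave detail to the full protocol, but here the formula itself is stated.

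**Conclusion.** The point holds in limited form. The scale-up rests on the constant unit cost that the protocol criticises elsewhere, and no planned analysis varies programme size or links the coverage scenarios to the projection. The product matches a programme's cost only at 100% coverage. It is 1.67, 1.25, 1.18 and 1.11 times the cost at 60%, 80%, 85% and 90% coverage, given the same unit cost and persons as the counting unit.

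The further error from growth in scale has no size or direction that the document determines; the figures in step 3 of the working are illustrations. The primary comparison of enhanced with annual MDA does not use the scale-up and is unaffected by it.

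**What to change.** In the scale-up text of Intervention costing, replace the single product with a projection from the ingredients database, for each enhanced strategy:

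fixed costs + (cost per community per round × communities × rounds) + (cost per treatment × people requiring antibiotics × stated coverage × treatments per person)

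- Report it at the 60%, 80% and 90% coverage levels already chosen under Economies of scale, so that the two sections are linked.
- State which costs are treated as fixed, and give a range for that share.
- State that a person treated is a unique person.
- Keep the linear product, if wanted, only as a scenario labelled as 100% coverage at constant unit cost.

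The quantities and prices are already to be recorded, and doses per participant are captured in both study arms, so no new data are needed. The cost is a little extra analysis and one explicit assumption about which costs are fixed.
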